## Abstract

**Background:**

Childhood intermittent exotropia [X(T)] is a type of strabismus (squint) in which one eye deviates outward at times, usually when the child is tired. It may progress to a permanent squint, loss of stereovision and/or amblyopia (reduced vision). Treatment options for X(T) include eye patches, glasses, surgery and active monitoring. There is no consensus regarding how this condition should be managed, and even when surgery is the preferred option clinicians disagree as to the optimal timing. Reports on the natural history of X(T) are limited, and there is no randomised controlled trial (RCT) evidence on the effectiveness or efficiency of surgery compared with active monitoring. The SamExo (Surgery versus Active Monitoring in Intermittent Exotropia) pilot study has been designed to test the feasibility of such a trial in the UK.

**Methods:**

Design: an external pilot patient randomised controlled trial.

Setting: four UK secondary ophthalmology care facilities at Newcastle NHS Hospitals Foundation Trust, Sunderland Eye Infirmary, Moorfields Eye Hospital and York NHS Trust.

Participants: children aged between 6 months and 16 years referred with suspected and subsequently diagnosed X(T). Recruitment target is a total of 144 children over a 9-month period, with 120 retained by 9-month outcome visit.

Randomisation: permuted blocks stratified by collaborating centre, age and severity of X(T).

Interventions: initial clinical assessment; randomisation (eye muscle surgery or active monitoring); 3-, 6- and 9-month (primary outcome) clinical assessments; participant/proxy completed questionnaire covering time and travel costs, health services use and quality of life (Intermittent Exotropia Questionnaire); qualitative interviews with parents to establish reasons for agreeing or declining participation in the pilot trial.

Outcomes: recruitment and retention rates; nature and extent of participation bias; nature and extent of biases arising from crossover or loss to follow-up; reasons for agreeing/declining participation; variability of cure rates (to inform power calculations for a definitive RCT); completion rates of outcome measures.

**Discussion:**

The SamExo pilot trial will provide important pointers regarding the feasibility of a full RCT of immediate surgery versus deferred surgery/active monitoring. The results of this pilot, including differences in cure rates, will inform the design of a definitive RCT.

**Trial registration:**

ISRCTN44114892

## Background

Strabismus, also known as squint, is an ophthalmic condition in which the eyes are misaligned and therefore look in different directions: that is, one eye looks straight ahead while the other turns either outward (exotropia), inward (esotropia), upward (hypertropia) or downward (hypotropia)
[1]. It may be constant, with loss of binocular function, or intermittent, with binocular function when the squint is not present. Squint can occur in children or adults and may have functional, aesthetic and psychosocial consequences
[2-16]. For example, teenagers and adults with squint have reported problems with self-esteem, self-image and interpersonal relationships, have met ridicule at school or work, and may attempt to avoid activities that bring attention to their condition or to develop strategies that conceal it
[8,10]. Similarly in young children, squint has been linked to lower psychosocial functioning, poorer interpersonal relationships and lower self-esteem
[15,16]. It has been shown that children as young as 5 years are significantly more likely to have negative social reactions to peers with strabismus
[13,14] and that teachers rate photographs of children with strabismus more negatively than those with straight eyes
[15].

Parents may seek treatment for their child’s squint out of concern that abnormal ocular alignment could result in social exclusion and bullying
[6]. However, conservative treatment with eye patches
[17-19] or glasses may in itself negatively affect the child’s psychosocial well-being and lead to increased bullying and stigmatisation
[6,11,20,21]. As Menon et al.
[8] report, these problems sometimes remain through to adulthood. Parents of children with squint may themselves experience a negative impact on their own psychological well-being, parental role, family functioning and general functioning
[22,23].

Intermittent exotropia [X(T)] is one of the commonest types of childhood strabismus
[24,25]. In this condition, one eye intermittently drifts outward. It is possible for X(T) to develop into a constant squint (XT)
[24,25] and lead to loss of stereovision and/or the development of amblyopia
[18] (reduced acuity in one eye caused by decreased quality visual input during the critical period of development). Typically, X(T) is first spotted in early childhood by parents noticing that their child’s eye is wandering outward as they look at objects in the distance or when they are very tired, inattentive or in bright sunlight.

Conservative treatment options for X(T) include occlusion with eye patches or wearing glasses that stimulate convergence. Eye muscle surgery can also be performed in order to realign the eyes. However, many clinicians and parents opt for an active monitoring approach, that is, they decide to wait and see whether the squint resolves spontaneously or at the very least does not deteriorate. Long-term natural history data are lacking, but there is some indication from observational work that X(T) surgery is more successful than conservative treatment and active monitoring in improving control of the eyes
[19]. However, the success of surgery is not guaranteed: it comes with a risk of over-correction whereby the eye alignment converts to a constant convergent deviation (esotropia) with a consequent loss of function in terms of stereovision and the potential to develop amblyopia in young children or diplopia (double vision) in older children. Alternatively, an under-correction may occur with persistence of the X(T). There is also evidence that the effectiveness of surgery declines over time
[26]. There is considerable variability in rates of surgery and a lack of consistency in the surgical indications for treatment of X(T) in the UK
[18,19]. Here, the majority of children with the condition do not appear to undergo eye muscle surgery within 2 years of presentation and instead are monitored recurrently, with significant loss to clinical follow-up.

Surgical intervention and active monitoring together incur substantial costs to the UK National Health Service (NHS). For example, over 6,000 procedures were performed by the NHS on children under 16 years in 2007/8, of which around 1,000 are estimated to have been performed for X(T). The tariff rate for strabismus surgery is £800, and together with approximately 100,000 clinic visits annually for review of patients with X(T) (at a tariff cost of £120 per new patient and £60 per review: estimated average new:review ratio 1:8), the total cost to the NHS alone is almost £7.5 million annually. With the inclusion of societal and family costs, the management of X(T) is more costly. Our previous cohort study
[18,19] has demonstrated not only considerable variability in management between centres, but also a ‘therapeutic inertia’, with many children receiving no active treatment and many eventually defaulting from follow-up, contributing to high DNA (did not attend) rates. Without further research, inefficiencies in the use of NHS and societal resources used to manage X(T) are likely to remain.

The lack of trial-based evidence means that the true effectiveness of treatment in ameliorating or curing the condition is unknown. Moreover, even when surgery is the preferred course of action there is little agreement on whether immediate surgery is more effective than delaying the operation for a specified length of time or until a certain age. A pressing need for carefully planned clinical trials of treatment to improve the evidence base for the management of this condition has previously been identified
[27].

The current investigators hope to conduct such a trial, if feasible. Since the recruitment phase in any trial is one of the most challenging
[28,29], and given the potential recruitment barriers particularly inherent in paediatric
[30-33] or surgical
[34] trials, we are first undertaking the SamExo (**S**urgery versus **A**ctive **M**onitoring in Intermittent **Exo**tropia) pilot trial in order to assess feasibility and inform the design and conduct of a full-scale trial (
http://research.ncl.ac.uk/samexo/).

Parents of children with X(T) participating in a previous observational cohort study [The Improving Outcomes in Intermittent Exotropia (IOXT) study]
[18,19] were surveyed and their comments taken into account in developing the present study, together with input from the lay group of the Royal College of Ophthalmologists and the patient and public engagement committee of the Newcastle NHS Hospitals Foundation Trust. Comments included the need to carefully explain the potential risks and benefits of a child with X(T) being in the active monitoring arm. Overall, comments were supportive of the need for such a study.

Our ultimate goal is to improve the treatment that children with X(T) receive by evaluating the risks and benefits of surgery in an RCT in which some children, where safe to do so, have surgical treatment deferred. Equally, the trial would enable us to determine whether some children get better spontaneously and to assess the effect of the condition and its treatment on quality of life (QOL). We would also evaluate costs to families and to the NHS and whether surgery represents a good use of the resources available.

The specific objectives of the current SamExo pilot trial are:

1. To determine whether participating centres are likely to recruit a sufficient number of patients to deliver a full trial.

2. To determine whether recruited patients will stay within their allocated groups and complete follow-up in sufficient numbers to deliver the trial.

3. To identify reasons why parents accept or decline participation in the trial.

4. To pilot the procedures involved in the trial including recruitment (giving information and obtaining consent), randomisation, intervention (surgery), masking, outcome measurements, and web-based trial management and data capture systems.

## Methods

### Study design

SamExo is a rehearsal pilot randomised controlled trial (RCT) to assess the feasibility of a full RCT of the effectiveness of surgical treatment against active monitoring in X(T) (Figure 
1). The trial is being conducted according to recommendations for good practice in pilot studies
[35].

**Figure 1 F1:**
[figure not shown]
SamExo pilot trial design.

### Study setting

Four secondary ophthalmology care facilities at the Newcastle upon Tyne NHS Foundation Trust (coordinating site), Sunderland Eye Infirmary, Moorfields Eye Hospital and York NHS Trust, each of which are large centres with specialist paediatric ophthalmology clinics.

### Participants and sample size

Children aged between 6 months and 16 years referred to the clinics with suspected X(T) from community screening, general practice or other health-care professionals, and subsequently diagnosed with X(T), as well as existing patients fulfilling the eligibility criteria. The parent/guardian provides written informed consent for participation in the study prior to any trial-specific procedures.

A formal power calculation was not performed for this feasibility study. It is not powered to detect a clinically or economically meaningful difference in the primary outcome between the surgical and active monitoring groups. Rather, the aim is to provide robust estimates of the likely rates of recruitment and retention, and to yield estimates of the variability of the primary and secondary outcomes to inform power calculations for a subsequent full-scale RCT. We originally estimated that over a recruitment period of 6 months (subsequently extended to 9 months) across four centres, we would be able to approach 240 patients who met the entry criteria. From their responses we would be able to determine whether the study is acceptable to parents and consequently whether it is possible to recruit patients and follow them up. We would also be able to estimate attrition rates. By approaching 240 children/parents we would be able to estimate the recruitment rate with a standard error no larger than 3.3%. Assuming that half of these children are actually recruited, we will be able to estimate the 6-monthly attrition rate with a standard error no larger than 4.3%.

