### Proposed outcome measures

For children with X(T), and their parents, the most relevant outcome from intervention is the restoration of normal eye alignment, with associated cosmetic and functional benefits. The primary outcome in a full-scale trial will therefore be the difference in the cure rate of X(T) between the surgical and actively monitored group; this is also the primary outcome for which data will be collected in the current pilot in order to inform sample size calculations for a definitive RCT. Cure will be defined as:

• a control score (NCS) of 0 (misalignment never noticed by parents, no observable deviation on cover test)

• demonstrable near stereoacuity in children over 3 years of age

Secondary outcomes include age-specific QOL assessments, median scores of control of exotropia assessed by parental report and clinical components of the NCS and the Mayo Score, rates of amblyopia, use of health-care resources, NHS costs, costs to families accessing the treatments being evaluated and incremental cost per cured patient (with cure as defined by the primary outcome), and a cost-consequences analysis based on the incremental cost with respect to changes in all relevant outcomes where possible.

The key outcomes of this pilot study are:

• data on the variability of the primary and secondary outcome measures;

• rates of participant recruitment and randomisation;

• nature and extent of participation bias;

• rates of cross-over and retention of recruited participants;

• nature and extent of biases arising from cross-over or loss to follow-up.

An initial recruitment rate of >60% and a retention rate of >70% will be considered necessary to indicate feasibility of a full-scale RCT.

Our intention in the full trial would be to conduct a cost-effectiveness analysis based on incremental cost per cured patient (as defined by the primary outcome) and a cost-consequences analysis based on incremental cost with respect to changes in all relevant outcomes where possible, including the QOL measure and different clinical measures. In the pilot study, we will rehearse this cost-effectiveness analysis to inform the study hypothesis and the analysis plan for the definitive trial. We will also assess the ease of collecting information on outcome and costs needed for the health economics analysis.

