## Discussion

The optimum management of X(T) in children is contentious, with some clinicians recommending early surgery, some preferring to delay and others choosing to actively monitor. The lack of robust evidence to guide management and the poorly understood natural history of this condition renders it difficult for clinicians to offer clear advice to parents. Consequently, many children are observed without any treatment for extended periods because of the uncertainty surrounding the best course of action. The need for evidence from randomised studies has been acknowledged for some time now
[27], and this is the first attempt, as far as we are aware, to explore the potential for a RCT of surgery versus active monitoring in childhood X(T). We felt it would be inappropriate to undertake a full-scale study involving large numbers of participants and centres before first conducting a feasibility study. The SamExo pilot study will provide important pointers regarding how acceptable a RCT of immediate surgery versus deferred surgery/active monitoring will be to participants and clinicians.

The recruitment phase will give us a good indication of the proportion of eligible children/parents who would sign up to a full trial, the likelihood of them withdrawing from it and also an idea of how many we would need to approach over a given duration to achieve a specified sample size.

Equally pivotal will be the reasons why parents agree or decline the pilot trial, their perceptions of the need for and purpose of randomisation, their views on the nature of the information they received, and suggestions for improving future trials and refining the research question. Findings from these qualitative interviews will not only inform the design of a possible full trial but may also help investigators planning studies of surgical interventions, trials of other children’s eye conditions or paediatric trials in general.

Potential ethical issues include the fact that some of the children in the SamExo pilot study will be asked to wait up to 9 months before being offered surgery. We feel that this can be justified as our previous work has shown that less than 8% of children with X(T) had surgery within the first year following initial assessment when treated in a routine setting
[18]; in some centres, no children had surgery within 2 years of diagnosis

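### The 3.3% standard error for the recruitment rate is a simple binomial figure for the four pilot centres; it does not bound the error for a full trial in many other centres

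*Protocol article*

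**What the plan says.** Under Participants and sample size, the protocol article does no power calculation and describes the purpose of the pilot in terms of estimation: "Rather, the aim is to provide robust estimates of the likely rates of recruitment and retention", together with outcome variability, to plan a later full-scale RCT. It expects that "across four centres, we would be able to approach 240 patients who met the entry criteria", and then gives two precision statements:

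- Recruitment: "By approaching 240 children/parents we would be able to estimate the recruitment rate with a standard error no larger than 3.3" per cent.
- Attrition, where the limit given is 4.3%: "Assuming that half of these children are actually recruited, we will be able to estimate the 6-monthly attrition rate with a standard error no larger".

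Neither statement mentions centre.

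Under Proposed outcome measures, the same two rates become feasibility criteria: "An initial recruitment rate of >60% and a retention rate of >70% will be considered necessary to indicate feasibility of a full-scale RCT". The Discussion says that recruitment will indicate what share of eligible families would join a full trial and how many would need to be approached. It describes that trial as much larger in both respects: "We felt it would be inappropriate to undertake a full-scale study involving large numbers of participants and centres before first conducting a feasibility study".

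**The concern.** The children approached come from four hospitals. A standard error computed as if they were one independent sample describes how well the pooled rate in those four hospitals is known. If the rate is then used to plan recruitment elsewhere, the choice of these four hospitals is a further source of error, and the printed figure leaves it out.

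There is some reason to expect centres to differ. The Background reports considerable variation between centres in how the condition is managed, and the Discussion notes that in some centres no child was operated on within two years of diagnosis. Willingness to be randomised to surgery could follow local practice. The four sites are also described under Study setting as large centres with specialist paediatric clinics, so they may not represent the centres a full trial would add.

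At stake is how far the pilot's rates can be carried into the full-trial projection. A reader who takes 3.3% as the error for that projection would plan the number of families to approach with too narrow a margin.

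**Working it through.** **Inputs.** From Participants and sample size: 240 approached, half of them recruited (120), four centres. From Proposed outcome measures: the 60% and 70% criteria. Assumed: equal centres (60 approached and 30 recruited in each) and the ICC, for which the documents give no value.

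**1. Reproduce the recruitment figure.** SE = sqrt(p(1−p)/n). At p = 0.5 and n = 240, sqrt(0.25/240) = 3.23%, within the stated 3.3%. No allowance for centre is included.

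**2. Reproduce the attrition figure.** At n = 120:

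- p = 0.5: sqrt(0.25/120) = 4.56%, above 4.3%
- p = 1/3: sqrt(0.2222/120) = 4.30%
- p = 0.30: sqrt(0.21/120) = 4.18%

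So 4.3% is binomial but not the maximum. It holds only if attrition is about one third or less. A true maximum of 4.3% needs n = 0.25/0.043² ≈ 135. The Abstract's target of 144 recruits would satisfy that (4.17%), but the sentence itself assumes half of 240.

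**3. Four centres as fixed strata.** With true centre rates of, for example, 40, 50, 60 and 70%, and 60 approached in each, SE = sqrt((0.24 + 0.25 + 0.24 + 0.21)/(60 × 16)) = sqrt(0.94/960) = 3.13%. For this target 3.3% stands and is slightly conservative.

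**4. A wider set of centres.** Multiply the binomial SE by sqrt(1 + (m−1) × ICC), with m = 60 for recruitment and m = 30 for attrition. The attrition column uses 30%, the complement of the 70% retention criterion.

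| Assumed ICC | Design effect, recruitment | Recruitment SE (p = 0.5) | Design effect, attrition | Attrition SE (p = 0.3) |
|---|---|---|---|---|
| 0 | 1.00 | 3.23% | 1.00 | 4.18% |
| 0.01 | 1.59 | 4.07% | 1.29 | 4.75% |
| 0.02 | 2.18 | 4.77% | 1.58 | 5.26% |
| 0.05 | 3.95 | 6.41% | 2.45 | 6.55% |

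To give the ICCs a scale: at p = 0.5 the between-centre SD is sqrt(0.25 × ICC), which is 5 points at 0.01 and about 11 points at 0.05.

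**5. When the stated bound fails.** Solving 3.23% × sqrt(1 + 59 × ICC) = 3.3% gives ICC ≈ 0.0008. For the wider target, almost any between-centre variation breaks the stated upper limit, though at so small an ICC the breach is trivial.

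**6. Uneven centres.** With an assumed split of 100/70/40/30, the effective m is (100² + 70² + 40² + 30²)/240 = 72.5. The recruitment SE is then 4.2% at ICC 0.01 and 6.9% at 0.05.

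**The case against.** The strongest reply is that the number is right for a target the document names. The first objective in the Background asks whether the participating centres can recruit enough patients, and for those centres step 3 shows that 3.3% holds. The sample-size section does not claim that it applies to centres outside the pilot. This stands, and it rules out calling 3.3% an arithmetic error. It does not remove the point, because the same section and the Discussion put the estimate to use in a trial with many centres.

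The second reply is that the size is assumed. The reported variation is in clinical management, not in parental consent and not in retention. All sites follow the same information and consent procedures. At ICC 0.01 the recruitment SE rises by less than one point. This also stands: the documents do not show that the ICC is as large as 0.05, and for attrition they offer no evidence of centre variation.

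The third reply concerns the consequence. A reader might infer that the feasibility decision rests on false precision. The documents do not support that. The 60% and 70% criteria are thresholds for the observed rates, described as necessary; the standard error does not enter them, and the chance of crossing them is the same whatever figure is printed. Crossover, participation bias and the parent interviews also inform feasibility.

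Finally, a centre-based interval from four centres would be very wide. With 3 degrees of freedom t = 3.18, so at a 60% rate the half-width is roughly 3.18 × 3.16 ≈ 10 points even at ICC 0, and 3.18 × 6.28 ≈ 20 points at ICC 0.05. Nor are the sites described as a random sample of centres. This limits the remedy.

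**Conclusion.** The concern holds in a limited form, and it is minor. The 3.3% is a correct simple binomial bound for the four pilot centres and is not a bound for the full-trial rate. For that wider use the maximum recruitment SE is about 4.1% to 6.4%, and the attrition SE at 30% attrition about 4.75% to 6.6%, if the ICC lies between 0.01 and 0.05 and centres are of equal size. The ICC range is an assumption and the true inflation could be smaller. Separately, the 4.3% for attrition is worded as an upper limit but is one only for attrition up to about one third. The documents do not support the stronger conclusions that the recruitment figure is miscalculated, that consent is known to vary by centre, or that the feasibility criteria are invalid.

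**What to change.** In Participants and sample size:

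- State that both standard errors are simple binomial figures for the four pilot centres.
- Add the wider range under a stated ICC assumption, for example 4.1% to 6.4% for recruitment at ICC 0.01 to 0.05, with the matching attrition figures.
- State that 4.3% assumes attrition of no more than about one third, or give 4.56% as the maximum at 120 recruited.

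In reporting, give recruitment and retention by centre with the between-centre range. Carry that range into the full-trial recruitment projection and into the discussion of the 60% and 70% criteria.

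Do not make those criteria depend on a t-interval or a random-centre model fitted to four centres, because the between-centre component is too poorly estimated. Use such an analysis at most as a sensitivity analysis.

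The cost is wording and a short table. Centre is already a stratification factor, so no extra patients or data are needed. The downside is that the stated precision looks less favourable.

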#### Primary outcome visit

The final assessment (9-month outcome) will be conducted by a research orthoptist (RO) who is masked to the allocation of the child and has not otherwise been in contact with children enrolled in the study. The parent and child will be requested not to reveal the group allocation of the child to the RO prior to the assessment. While children have noticeably red eyes immediately following eye muscle surgery, it is recognised that this redness resolves within 6 weeks when this is a first procedure. Residual scarring of the conjunctiva following eye muscle surgery will be inconspicuous by 6 months.

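### With 120 recruited, the maximum standard error for attrition is 4.6%, not the stated 4.3%; the effect is minor, and the sentence needs either a corrected figure or a stated condition

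*Protocol article*

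**What the plan says.** The Participants and sample size section says that no formal power calculation was done and gives two precision statements in its place. The first concerns recruitment: "By approaching 240 children/parents we would be able to estimate the recruitment rate with a standard error no larger than 3.3" per cent. The second concerns attrition. It sets its base with "Assuming that half of these children are actually recruited" and claims that the trial can "estimate the 6-monthly attrition rate with a standard error no larger than 4.3" per cent. Half of 240 is 120. The section gives no assumed attrition rate and no ceiling on it.

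Three other statements bear on this:

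- The Methods part of the abstract gives the target: "Recruitment target is a total of 144 children over a 9-month period, with 120 retained by 9-month outcome visit".
- The same part gives the visit schedule: "3-, 6- and 9-month (primary outcome) clinical assessments".
- The Proposed outcome measures section gives the feasibility criteria: "An initial recruitment rate of >60% and a retention rate of >70% will be considered necessary to indicate feasibility" of the full trial.

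**The concern.** A standard error described as no larger than some value is an upper bound. With no restriction on the attrition rate, it has to hold at the worst case, which for a proportion is 50%. With 120 children the worst case exceeds 4.3%, so the figure does not follow from the inputs printed beside it.

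Retention is one of the two rates on which the pilot judges feasibility, and estimating it well is a stated aim. A reader planning the full trial, or a similar pilot, would take the printed precision at face value. The sentence also uses a recruited base (120) that differs from the abstract's target (144), and it describes a 6-monthly rate while the retention target is set at the 9-month visit. Anyone correcting the figure has to settle the base first.

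**Working it through.** **Inputs.** From Participants and sample size: 240 approached, half recruited (n = 120), and stated bounds of 3.3% for recruitment and 4.3% for attrition. From the abstract: 144 recruited and 120 retained at 9 months. From Proposed outcome measures: retention above 70%, so attrition below 30%.

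**Formula.** SE = sqrt(p(1 − p)/n), largest at p = 0.5, where it equals sqrt(0.25/n).

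**Recruitment figure.** n = 240: sqrt(0.25/240) = 3.23%. The stated bound of 3.3% holds.

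**Attrition figure.** n = 120: sqrt(0.25/120) = 4.56%. The stated 4.3% is not reproduced.

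**Attempts to recover 4.3% at p = 0.5**

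| Variant | Maximum SE |
|---|---|
| n = 120 | 4.56% |
| n − 1 = 119 in the denominator | 4.58% |
| n + 4 = 124 (Agresti–Coull) | 4.49% |
| Finite-population correction, 120 of 240 | 3.23% |
| n = 144 (abstract target) | 4.17% |

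None gives 4.3%. A maximum of 4.3% needs n = 0.25/0.043² = 135.2, so 136 recruits, a number that does not appear in the article.

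**Where the bound fails with n = 120.** Setting p(1 − p)/120 = 0.043² gives p(1 − p) = 0.2219, so p = 0.332 or 0.668. The standard error exceeds 4.3% between these values and is within the bound outside them.

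**Standard error at particular attrition rates**

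| Attrition | n = 120 | n = 144 |
|---|---|---|
| 16.7% (24/144, implied by the target) | 3.40% | 3.11% |
| 20% | 3.65% | 3.33% |
| 30% (feasibility limit) | 4.18% | 3.82% |
| 33.3% | 4.30% | 3.93% |
| 40% | 4.47% | 4.08% |
| 50% (maximum) | 4.56% | 4.17% |

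**Size.** The worst-case shortfall is 4.56 − 4.30 = 0.26 percentage points. As a 95% half-width, 1.96 × 4.56 = 8.9 points against 1.96 × 4.3 = 8.4 points.

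**Recruited base.** 0.5 × 240 = 120 and 0.6 × 240 = 144. The abstract's target therefore equals 60% of the 240 approached, the same percentage as the recruitment criterion, although the article does not say that it was derived in this way.

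**The case against.** The best defence is that 4.3% is a conditional bound whose condition was lost when the protocol was condensed. With attrition of one third, sqrt((1/3)(2/3)/120) = 4.30%, which matches the printed figure. A ceiling of one third would be reasonable for a trial that needs attrition below 30%. This is a plausible origin, but the article states no ceiling. The point that stands is that stating one would be a legitimate repair.

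A second defence is that, if 144 is the true base, the maximum is 4.17% and the claim of no more than 4.3% is literally correct. That is so, but the error then moves to the word half, because 144 is 60% of 240.

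A third is that the discrepancy has no consequence. This largely stands: the bound fails only at attrition rates that already miss the retention criterion.

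Three stronger readings are tempting, and the document does not support them:

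- A reader might infer that the precision is given for the wrong time point. There is a 6-month visit, so 6-month attrition can be estimated, and the maximum standard error depends on n and p, not on months. What can be said is that no precision is given for 9-month attrition, the quantity to which the retention target refers.
- A reader might infer that these two standard errors are the whole justification of the sample size. The section also cites estimating the variability of the outcomes, and the article gives a recruitment target and explicit feasibility thresholds.
- A reader might infer that the recruitment figure proves a worst-case method that the attrition figure then breaks. The worst case for 240 is 3.23%, which would round to 3.2%. The printed 3.3% is consistent with that method but does not show that it was used.

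**Conclusion.** The stated bound is wrong as written. For the 120 recruits that the sentence assumes, and with no restriction on attrition, the maximum standard error is 4.56%, and 4.3% is exceeded for attrition between about 33% and 67%. The effect is minor: at most 0.26 percentage points on the standard error, or about half a point on a 95% half-width. At the feasibility limit of 30% attrition the standard error is 4.18%, inside the stated bound, so no threshold or feasibility decision changes.

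This rests on the simple binomial standard error, on 120 being the denominator for attrition, and on the absence of any stated ceiling on attrition. If either of the last two was meant otherwise, the figure can be defended, but the sentence must then say so.

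**What to change.** Restate the one sentence in one of three ways:

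1. Keep 120 recruited and give the maximum standard error as 4.6%.
2. Keep 120 recruited and 4.3%, and add that this assumes attrition of no more than about one third.
3. If the abstract's target of 144 is the intended base, replace half by 60% and give 4.2%.

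In each case, preferably describe the rate as attrition at the 9-month visit, to match the retention target, and make the recruited base agree with the abstract.

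The cost is one sentence. Under the first option the stated precision becomes slightly less favourable; under the third it becomes slightly more favourable. No change to design, target or criteria is needed.
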